### **1.16 Ethics Consideration**

#### **1.16.1 Ethical Approval for conducting study**

Prior to commencing data collection of the study, ethical approval and permission will be requested and obtained from Medical Review and Ethics Committee (MREC), Ministry of health Malaysia. Following that, a written permission to conduct the study in government health clinic in Malacca will be obtained from the Director of Malacca state health department. On top of that, written inform consent will be obtain from each individual respondent before participating in the study (voluntary participation).

Upon MREC approval, the Ethics Committee for Research Involving Human Subject Universiti Putra Malaysia (*Jawatankuasa Etika Untuk Penyelidikan Melibatkan Manusia Universiti Putra Malaysia -JKEUPM*) will notify.

#### **1.16.2 Confidentiality**

During the questionnaire answering session, the identification of the questionnaire will be conducted by assigning code number, no individual name or any other official identification of respondent will be written in the questionnaire. The intervention and questionnaire answering session will be conducted at a separate suitable place away from the MMT counter to maintain confidentiality of respondents. The answered questionnaire will be kept in an envelope which was labelled as “confidential” in a locked file cabinet by the assigned site interviewer and will be handed over to the investigator at an assigned date. The confidentiality of the information gain will be maintained, and the identification information will be kept anonymous throughout data analysis.

#### **1.16.3 Duration and means of storage and archival of medical records and study data**

Questionnaire will be kept in a secure locked file cabinet with locking mechanism and only the principal investigator will have the key to the locker and have access to the questionnaire. The data will enter into SPSS software and access to the data will be encrypted with password to ensure safety and confidentiality of the data. Only the principal investigator will have access to the data. The study data will be kept for 5 years after final publication and only be used particularly for the current study. After the period of storage, the written questionnaires will be shredded, and the electronic data will be deleted.

#### **1.16.4 Respondent access to the personal information and study data**

Respondent will not be given access to the personal information and study data. The personal information and study data will be kept confidential and only the principal investigator will have access to the information and data. The data will be analyzed collectively and not by individually.

#### **1.16.5 Publication policy and confidentiality of subject's personal information**

All patient details and information obtained from the study will be kept confidential and used only for the research purposes. No identifying information will be recorded in the questionnaire. Each questionnaire will be assigned a unique code number and a separate electronic sheet containing respondent name list matched with the unique code number will be kept securely in a password-protected laptop and accessible only to the principal investigator. No personal information of the subject respondent will be published. Permission from the Director General of Health, Malaysia, or relevant authorities will be obtained prior to publication. Future publication will be based on the collective data analysis, not individual data analysis. The respondent can request the published findings by referring to the final published article on the research.

## APPENDICES

### APPENDIX A: QUESTIONNAIRE

#### Section A: Sociodemographic

You are required to answer each question listed. For multiple answer questions, please select one (1) best answer by ticking (✓).

| No | Item              | Answer                                                                                                                                                              |
|----|-------------------|---------------------------------------------------------------------------------------------------------------------------------------------------------------------|
| 1  | Age               | _____ year (Please Specify)                                                                                                                                         |
| 2  | Gender            |  Male
 Female                                                                                                    |
| 3  | Race              |  Malay
 Chinese
 Indian
 Others_____ (Please Specify)      |
| 4  | Marital Status    |  Single
 Married
 Split up (Not living together)
 Divorced |
| 5  | Employment Status |  Have permanent job
 No permanent job
 Not working                                    |
| 6  | Monthly Income    | RM_____ (Please state)                                                                                                                                              |

|   |                 |                                                                                                                                                                                                            |
|---|-----------------|------------------------------------------------------------------------------------------------------------------------------------------------------------------------------------------------------------|
| 7 | Education level |  No formal education
 Primary school
 Secondary school
 University/College/Institution (Tertiary) |
|---|-----------------|------------------------------------------------------------------------------------------------------------------------------------------------------------------------------------------------------------|

### Section B: Methadone Treatment Profile

You are required to answer each question listed.

| No | Item                                       | Answer                                      |
|----|--------------------------------------------|---------------------------------------------|
| 1  | Current Methadone Dose                     | _____mg/day                                 |
| 2  | Duration from start of Methadone treatment | Year of starting Methadone treatment: _____ |

### Section C: HIV and Hepatitis C status

You are required to answer each question listed. Please answer the following statements regarding HIV and hepatitis C testing and status. Please tick (✓) your answer in the space provided.

| No | Items                                                         | Answer |    |          |
|----|---------------------------------------------------------------|--------|----|----------|
|    |                                                               | Yes    | No | Not Sure |
| 1  | Have you ever tested for hepatitis C?                         |        |    |          |
| 2  | Have you test for hepatitis C last year?                      |        |    |          |
| 3  | Do you have hepatitis C?                                      |        |    |          |
| 4  | Have you ever tested for HIV?                                 |        |    |          |
| 5  | Have you test for HIV last year? (Only for those without HIV) |        |    |          |
| 6  | Do you have HIV?                                              |        |    |          |

#### Section D: History of hepatitis C educational program

Please determine the following statements on hepatitis C educational program. Please tick (✓) your answer in the space provided.

| No | Items                                                                      | Answer |    |          |
|----|----------------------------------------------------------------------------|--------|----|----------|
|    |                                                                            | Yes    | No | Not Sure |
| 1  | Have you ever participated in any form of hepatitis C educational program? |        |    |          |

#### Section E: Drug and alcohol use history

Please determine the following statements on drug and alcohol use. Please tick (✓) your answer in the space provided.

##### Drug Use

| No | Items                                                                            | Answer |    |
|----|----------------------------------------------------------------------------------|--------|----|
|    |                                                                                  | Yes    | No |
| 1  | Have you ever used injecting drug?                                               |        |    |
| 2  | If yes, do you have history of injecting drugs use during the last 6 months?     |        |    |
| 3  | Have you ever used non-injecting drug?                                           |        |    |
| 4  | If yes, do you have history of non-injecting drugs use during the last 6 months? |        |    |

##### Alcohol Use

| No | Items                                                                                      | Answer |    |
|----|--------------------------------------------------------------------------------------------|--------|----|
|    |                                                                                            | Yes    | No |
| 1  | Have you ever consumed alcohol in the past 1 year? (If yes, proceed to question 2 until 5) |        |    |
| 2  | Have you ever felt you should cut down on your drinking?                                   |        |    |
| 3  | Have people annoyed you by criticizing your drinking?                                      |        |    |
| 4  | Have you ever felt bad or guilty about your drinking?                                      |        |    |

|   |                                                                                                                      |  |  |
|---|----------------------------------------------------------------------------------------------------------------------|--|--|
| 5 | Have you ever had a drink first thing in the morning to steady your nerves or to get rid of a hangover (eye-opener)? |  |  |
|---|----------------------------------------------------------------------------------------------------------------------|--|--|

### Section F: Knowledge on hepatitis C

Please determine whether the following statements hepatitis C infection are true, ~~false~~ or not sure. Please tick (✓) your answer in the space provided.

| No | Statements                                                                            | Answer options |       |          |
|----|---------------------------------------------------------------------------------------|----------------|-------|----------|
|    |                                                                                       | True           | False | Not Sure |
| 1  | Hepatitis C is caused by a virus                                                      |                |       |          |
| 2  | Hepatitis C is spread by sharing needles for drugs                                    |                |       |          |
| 3  | Hepatitis C is mainly spread by unprotected sex                                       |                |       |          |
| 4  | A person can get hepatitis C by getting a tattoo or piercing                          |                |       |          |
| 5  | A person can get hepatitis C by sharing personal material like razors or toothbrushes |                |       |          |
| 6  | To be certain of a hepatitis C infection, a blood test is necessary                   |                |       |          |
| 7  | Hepatitis C damages the liver and can cause liver failure                             |                |       |          |
| 8  | Hepatitis C can lead to liver cancer                                                  |                |       |          |
| 9  | Some people can live many years without symptoms                                      |                |       |          |
| 10 | Part of the people infected with the hepatitis C virus can cure spontaneously         |                |       |          |
| 11 | Drinking a lot of alcohol is a good idea for someone with hepatitis C                 |                |       |          |
| 12 | There is a vaccine to prevent hepatitis C                                             |                |       |          |
| 13 | The treatment for hepatitis C cures everyone who is treated                           |                |       |          |
| 14 | The treatment for hepatitis C currently consists of injections and taking pills       |                |       |          |
| 15 | The treatment for hepatitis C <del>has to</del> be taken lifelong                     |                |       |          |
| 16 | The treatment for hepatitis C can cause side effects like depression                  |                |       |          |

|    |                                                                                                   |  |  |  |
|----|---------------------------------------------------------------------------------------------------|--|--|--|
| 17 | Substitution treatment can be followed during hepatitis C treatment                               |  |  |  |
| 18 | Once you completed a treatment for hepatitis C, a reinfection is impossible because you're immune |  |  |  |
| 19 | If you have hepatitis C it is not necessary to get a vaccination for hepatitis A or B             |  |  |  |

### Section G: Attitude towards hepatitis C infection and treatment

Please indicate your level of agreement with each of the statements below by selecting and marking (✓) at your answer choice in the space provided based on the provided scale.

Question 1: Based on Important scale below

| No | Statement                                                                                             | Not Important | Slightly Important | Moderately Important | Important | Very Important |
|----|-------------------------------------------------------------------------------------------------------|---------------|--------------------|----------------------|-----------|----------------|
| 1  | If you were diagnosed with hepatitis C, how important is it for you to get treatment for hepatitis C? |               |                    |                      |           |                |

Question 2-10: For question 2 to 10, the scale as follow:

|                   |          |         |       |                |
|-------------------|----------|---------|-------|----------------|
| 1                 | 2        | 3       | 4     | 5              |
| Strongly disagree | Disagree | Neutral | Agree | Strongly Agree |

| No | Statement                                                                     | 1 | 2 | 3 | 4 | 5 |
|----|-------------------------------------------------------------------------------|---|---|---|---|---|
| 2  | 'I do not think that I need to take medication for my hepatitis C'.           |   |   |   |   |   |
| 3  | 'I don't believe that I will die from hepatitis C'.                           |   |   |   |   |   |
| 4  | 'Treating my other illnesses is more important than treating my hepatitis C'. |   |   |   |   |   |

|    |                                                                                                       |  |  |  |  |  |
|----|-------------------------------------------------------------------------------------------------------|--|--|--|--|--|
| 5  | 'Treating hepatitis C will make my life better'.                                                      |  |  |  |  |  |
| 6  | 'Hepatitis C does not cause any problems in my body'.                                                 |  |  |  |  |  |
| 7  | I do not think I need treatment for hepatitis C because I can't tell that I have it' (Asymptomatic)   |  |  |  |  |  |
| 8  | 'Feeling ashamed of having hepatitis C makes me uncomfortable seeking hepatitis C treatment or care'. |  |  |  |  |  |
| 9  | 'People may treat me differently if they know that I have hepatitis C'.                               |  |  |  |  |  |
| 10 | 'I am scared about what might happen to me because I have hepatitis C'.                               |  |  |  |  |  |

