### **1.2.2 Specific Objectives**

The specific objectives of this study are:

- i. To develop and implement a Theory of planned behaviour-based hepatitis C education intervention module to increase willingness to hepatitis C treatment.
- ii. To identify the sociodemographic characteristics, MMT treatment profile, HIV and hepatitis C status, alcohol use, drug history and history of attending hepatitis C educational program of the respondents in the intervention and control group at baseline.
- iii. To evaluate the effectiveness of Theory of planned behaviour-based hepatitis C education intervention module in improving willingness for hepatitis C treatment among MMT clients in Malacca.
  - i. Within intervention group and within control group from baseline to immediately post-intervention and 3 months post-intervention.
  - ii. Between groups (intervention group and control group) at baseline, immediately post-intervention, and 3 months post-intervention.
  - iii. Within and between groups over time.
- iv. To evaluate the effectiveness of Theory of planned behaviour-based hepatitis C education intervention module in improving knowledge, attitude towards

behaviour, subjective norms, and perceived behavioural control for hepatitis C treatment among MMT clients in Malacca.

- i. Within intervention group and within control group from baseline to immediately post-intervention and 3 months post-intervention.
- ii. Between groups (intervention group and control group) at baseline, immediately post-intervention, and 3 months post-intervention.
- iii. Within and between groups over times.

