### **1.3 Research Hypotheses**

The research hypotheses of this study are:

**H1-** There is higher willingness for hepatitis C treatment within group and between group in intervention group compared to the control group at immediate and 3 months post-intervention.

**H2-** There is higher knowledge for hepatitis C within group and between group in intervention group compared to the control group at immediate and 3 months post-intervention.

**H3-** There is higher positive attitude towards hepatitis C infection within group and between group in intervention group compared to the control group at immediate and 3 months post-intervention.

**H4-** There is higher positive hepatitis C related subjective norms within group and between group in intervention group compared to the control group at immediate and 3 months post-intervention.

**H5-** There is higher hepatitis C related perceived behavioural control within group and between group in intervention group compared to the control group at immediate and 3 months post-intervention.

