#### **1.7.3 Selection Criteria**

##### **1.7.3.1 Inclusion Criteria**

The inclusion criteria are:

- i. Age 18 years and above
- ii. Active MMT clients of government health clinics in Malacca

- iii. Negative hepatitis C status or positive hepatitis C status but not on treatment.

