#### 1.7.3.2 Exclusion Criteria

The exclusion criteria are:

- i. MMT clients diagnosed with hepatitis C and ever or currently on treatment regardless of the sustained virologic response (SVR) status.
- ii. MMT clients currently involve in any intervention studies or involved in any intervention study completed within one year before initiation of this study.

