This section will explore regarding respondent attitude on hepatitis C infection. The questionnaire in this section will be adopted from previous study (Chen et al., 2013). Total item in this scale are 10 items. For first question of this section, 5-point important scale will be apply in which respondent will need to choose from Not important to very important option. For question 2 until 10, the level of agreement of respondent will be rated using 5-point Likert scale ranging from 1 as "strongly disagree" to 5 as "strongly agree". For this section, the total score will

range from 10 to 50. The higher the score indicate the more positive attitude towards hepatitis C infection.

ix. Section I for subjective norm

This section explores regarding clients perceived social pressure on willingness to hepatitis C treatment. This section will be consist of 4 items and the items will be adopted from guidelines on TPB questionnaire (Francis et al., 2004). The level of agreement of respondent will be rated using 7-point scale ranging from 1 as “strongly disagree” to 7 as “strongly agree”. For this section, the total score will range from 4 to 28. The higher the score indicate the more positive subjective norm on willingness for hepatitis C treatment.

x. Section J for perceived behavioural control

This section explores regarding clients perceived behavioural control on willingness to hepatitis C treatment. It explore on perceived ease or difficulty of performing the behaviour and it is assumed to reflect past experience as well as anticipated impediments and obstacles (Ajzen, 1991). This section will be consist of 4 items and the items will be adopted from guidelines on TPB questionnaire (Francis et al., 2004). The level of agreement of respondent will be rated using 7-point scale ranging from 1 as “strongly disagree” to 7 as “strongly agree”. For this section, the total score will range from 4 to 28. The higher the score indicate the more positive perceived behavioral control on willingness for hepatitis C treatment.

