### Section J: Willingness for hepatitis C treatment

Based on the statements below, **circle** your answer of choice in the space provided

| Question                                                                                                                                                                       | Answer |    |
|--------------------------------------------------------------------------------------------------------------------------------------------------------------------------------|--------|----|
| Suppose you were diagnosed to have hepatitis C and was advised for hepatitis C treatment by the medical officer, are you willing to received hepatitis C treatment as advised? | Yes    | No |

THE END

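### Six of the ten attitude items presuppose that the respondent has hepatitis C, although uninfected clients are eligible, so the attitude total is hard to interpret for them

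*Protocol*

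**What the plan says.** **Who may enrol.** Protocol 1.7.3.1 sets the status criterion as "Negative hepatitis C status or positive hepatitis C status but not on treatment". Section 1.7.3.2 then removes "MMT clients diagnosed with hepatitis C and ever or currently on treatment", which raises the share of negatives among those left.

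**What is claimed.** Objective iv (1.2.2) is to show an effect "in improving knowledge, attitude towards" behaviour, norms and control among methadone clients in general. H3 (1.3) reads "There is higher positive attitude towards hepatitis C infection within group and between group in intervention group compared to the control group". Neither is confined to infected clients.

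**How attitude is measured.** Section 1.10.2 says "Total item in this scale are 10 items" and gives one total from 10 to 50, higher being more positive, for everyone. The items are in Appendix A under Section G (1.10.2 calls the same scale Section H). Item 1 assumes a diagnosis for the sake of the question. Items 2 to 10 carry no such stem. Two examples are "I do not think that I need to take medication for my hepatitis C" and "I am scared about what might happen to me because I have hepatitis C". The form has no instruction to imagine being infected and no option for not applicable, and 1.10.2 gives no scoring rule by infection status.

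**How the neighbouring scales do it.** The willingness question opens "Suppose you were diagnosed to have hepatitis C and was advised for hepatitis C treatment by the medical officer". All eight norms and control items (Appendix A, Sections H and I) are likewise tied to a possible diagnosis.

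**The concern.** An uninfected client who would readily accept treatment if diagnosed can truthfully agree that he needs no medicine for a hepatitis C he does not have, and that the disease is doing nothing to his body. Items about shame or fear over his own infection have no natural answer for him. His responses follow his infection status, and reverse scoring cannot turn them into a measure of attitude.

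Attitude is a named secondary outcome with its own hypothesis. If a sizeable part of the sample cannot express an attitude through most of the items, the score carries extra noise and responds less to the module. A null or small result on H3 would then be hard to read. A positive one could not be described as a change of attitude in all clients.

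**Working it through.** **1. Score range.** Ten items scored 1 to 5 give 10 × 1 = 10 to 10 × 5 = 50. This reproduces the range in 1.10.2. Each item contributes 5 − 1 = 4 points of spread, 40 in total.

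**2. Item by item (Appendix A, Section G, paraphrased).**

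| Item | Subject | Presupposes infection? |
|---|---|---|
| 1 | Importance of treatment, given a supposed diagnosis | No, hypothetical |
| 2 | Need for medicine for one's own infection | Explicitly |
| 3 | Belief about dying of the disease | No, anyone can answer |
| 4 | Other illnesses ranked above one's own infection | Explicitly |
| 5 | Whether treatment will improve one's life | By implication |
| 6 | Whether the disease troubles one's body | By implication |
| 7 | No need for treatment because the infection goes unnoticed | Explicitly |
| 8 | Shame at being infected as a barrier to care | Explicitly |
| 9 | Different treatment by others who know of one's infection | Explicitly |
| 10 | Fear of what being infected may bring | Explicitly |

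Six are explicit: 6 × 4 = 24 of 40 points of spread, or 60%. With items 5 and 6 there are eight: 32 of 40, or 80%.

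**3. How many respondents.** The protocol gives no expected mix, so this is an illustration. Inputs:
- 64.6% of methadone clients diagnosed with hepatitis C in a national study (Protocol 1.1), so 1 − 0.646 = 0.354 not diagnosed;
- planned sample 236 (1.7.6);
- an assumed share *t* of positives excluded as ever treated (1.7.3.2).

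Negative share = 0.354 / (0.354 + 0.646 × (1 − *t*)).

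| *t* (assumed) | Calculation | Negative share | Of 236 |
|---|---|---|---|
| 0 | 0.354 / 1.000 | 35% | about 84 |
| 0.10 | 0.354 / 0.935 | 38% | about 89 |
| 0.25 | 0.354 / 0.8385 | 42% | about 100 |
| 0.50 | 0.354 / 0.677 | 52% | about 123 |

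**4. Which outcomes are affected.** The knowledge items are statements of fact. Norms, control and willingness are framed around a possible diagnosis. The mismatch is confined to attitude.

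**The case against.** **The pretest may catch it.** Section 1.11.2 plans cognitive debriefing to find conceptually unsuitable items, and 1.11.2.2 adds expert ratings of relevance and clarity. The Malay form actually used is not shown. This mitigates the point. But no step calls for hepatitis C-negative respondents or raises this mismatch, and the unconditional wording stands in Appendix A.

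**Respondents may cope.** Item 1 sets a hypothetical frame just before, the scale offers neutral and disagree, and item 9 contains an *if*. Some uninfected clients may indeed answer as if infected, but nothing tells them to, so the total would mix two readings. The *if* in item 9 concerns what others know, not whether the respondent is infected.

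**Stronger readings that a reader might infer, and that do not hold:**

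- *Nine of ten items presuppose infection.* Nine lack a conditional stem. Six presuppose infection explicitly and two more by implication; item 3 is open to anyone.
- *Objective iv cannot be answered.* Only its attitude part is touched.
- *The trial comparison is biased.* Both arms get the same form and are randomised. A chance imbalance in infection status would enter the unadjusted single-time-point tests in 1.15.1. A constant level difference would already be there at baseline and would largely drop out of the group-by-time comparison in the mixed model.
- *Education would push uninfected clients' answers the wrong way.* Table 3.2 includes no testing and no disclosure of status, so the module content does not support this.
- *The effect shrinks to about 65% of its true size or less.* The figure 1 − 0.354 = 0.646 assumes that uninfected clients' answers to the affected items cannot move at all, on an assumed mix. It is a limiting case, not an estimate.
- *An uninfected client loses 20% of the score range.* Strong agreement with items 2 and 6 would cost 2 × 4 = 8 of 40 points only if both are reverse-scored, which 1.10.2 does not state. It would in any case be a shift in level common to both arms.

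**Conclusion.** The point holds for one secondary scale. Six attitude items explicitly, and eight with implication, ask about the respondent's own hepatitis C, while clients without it are eligible and receive the same 10 to 50 total. For them the total partly reflects infection status, so H3 and the attitude part of objective iv lose interpretability and sensitivity. The randomised comparison remains valid, and the knowledge, norms, control and willingness outcomes are unaffected.

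The size cannot be fixed from the protocol. The range of about 35% to 52% uninfected rests on two assumptions: that the cited 64.6% carries over to Malacca, and that between none and half of the positives are excluded as ever treated. The 64.6% counts people diagnosed, so its complement includes some undiagnosed infections. It is a rough guide to clients with no known infection, who face the same difficulty with these items. How far their answers fail to respond to the module is unknown. This is a worthwhile and cheap correction, not a threat to the primary result.

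**What to change.** **Before the pretest in 1.11.2:** put items 2 to 10 under the conditional stem that item 1 already uses, for example *If I were diagnosed with hepatitis C, I do not think I would need medicine for it*. Use the same wording at baseline, immediately after the intervention and at three months. Include hepatitis C-negative clients in the cognitive debriefing. The cost is rewording nine items and a small departure from the source scale, which is already being translated and re-validated.

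**If data were already collected with the current wording** (1.13 is written in the past tense, so this is possible):
- keep the intention-to-treat analysis of all participants, as 1.15.2 requires;
- add baseline hepatitis C status from Appendix A, Section C as a covariate in the attitude model, keeping the not-sure answer as its own category;
- report the attitude effect by status as a sensitivity analysis;
- state that the attitude score has limited meaning in hepatitis C-negative clients.

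Restricting H3 to self-reported positives as the main analysis is not advised. It would drop randomised participants, contrary to 1.15.2, and rest on a self-report that allows not sure. The analysis changes cost one covariate and one extra table; the subgroup estimates will be imprecise and should be labelled as such.
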